# Respiratory support in COPD patients after acute exacerbation with monitoring the quality of support (Rescue2-monitor): an open-label, prospective randomized, controlled, superiority clinical trial comparing hospital- versus home-based acute non-invasive ventilation for patients with hypercapnic chronic obstructive pulmonary disease

**DOI:** 10.1186/s13063-020-04672-w

**Published:** 2020-10-22

**Keywords:** Chronic obstructive pulmonary disease (COPD), Non-invasive ventilation (NIV), Hypoventilation, Targeted treatment, Hypercapnic respiratory failure

## Abstract

Chronic obstructive pulmonary disease (COPD) is expected to be the 3^rd^ leading cause of death worldwide by 2020. Despite improvements in survival by using acute non-invasive ventilation (NIV) to treat patients with exacerbations of COPD complicated by acute hypercapnic respiratory failure (AHRF), these patients are at high risk of readmission and further life-threatening events, including death. Recent studies suggested that NIV at home can reduce readmissions, but in a small proportion of patients, and with a high level of expertise. Other studies, however, do not show any benefit of home NIV. This could be related to the fact that respiratory failure in patients with stable COPD and their response to mechanical ventilation are influenced by several pathophysiological factors which frequently coexist in the same patient to varying degrees. These pathophysiological factors might influence the success of home NIV in stable COPD, thus long-term NIV specifically adapted to a patient’s “phenotype” is likely to improve prognosis, reduce readmission to hospital, and prevent death. In view of this conundrum, Rescue2-monitor (R2M), an open-label, prospective randomized, controlled study performed in patients with hypercapnic COPD post-AHRF, will investigate the impact of the quality of nocturnal NIV on the readmission-free survival. The primary objective is to show that any of 3 home NIV strategies (“rescue,” “non-targeted,” and “targeted”) will improve readmission-free survival in comparison to no-home NIV. The “targeted” group of patients will receive a treatment with personalized (targeted) ventilation settings and extensive monitoring. Furthermore, the influence of comorbidities typical for COPD patients, such as cardiac insufficiency, OSA, or associated asthma, on ventilation outcomes will be taken into consideration and reasons for non-inclusion of patients will be recorded in order to evaluate the percentage of ventilated COPD patients that are screening failures. ClinicalTrials.gov NCT03890224. Registered on March 26, 2019.

## Background

According to the Global Burden of Disease (GBD), chronic obstructive pulmonary disease (COPD) is the third leading cause of death worldwide, something that WHO had not predicted to occur until 2030 [1] and is expected to become the leading cause of death in the next 15 years [2]. Respiratory failure due to severe acute exacerbations is now recognized as an independent negative prognostic factor with mortality increasing with the frequency of severe exacerbations.

Respiratory failure in patients with stable COPD and their response to mechanical ventilation are influenced by several pathophysiological factors, such as ventilation/perfusion ratio, obesity, and its relation to hypoventilation, muscle function/myopathy, and comorbidities, such as obstructive sleep apnea hypopnea syndrome (OSAHS) and/or chronic heart failure [3]. Thus, every patient is different, because many of these factors coexist in the same patient to varying degrees.

Although there is no evidence that “targeted” treatments are more effective, it follows that the success of home non-invasive ventilation (NIV) in stable COPD may be largely influenced by the main underlying pathophysiological process. Therefore, long-term home NIV, specifically adapted to the patients “phenotype”, is likely to improve prognosis, reduce readmission to hospital or death in COPD patients who remain persistently hypercapnic, and thus result in a more equilibrated clinical situation for the patients.

Already in the 1960s, clinicians speculated that home intermittent respiratory muscle rest afforded by negative-pressure ventilators might also benefit daytime respiratory muscle performance of patients with severe COPD [4]. This approach was, however, generally abandoned in the early 1990s after a large randomized clinical trial nocturnally using a “jacket” negative-pressure ventilator showed no improvement in exercise endurance or respiratory muscle strength in patients with severe COPD, and acceptance of the device by patients was poor [5]. Subsequent studies using home NIV have reported conflicting results with negative findings [6, 7], a slight improvement in quality of life [8], improvements in dyspnea and sleep [9], or reduced mortality, but in association with worse quality of life [10]. Thus, the 2013 Cochrane review of long-term NIV for COPD concluded that there was no evidence of significant benefit in any of the measured indices [11].

Despite the improvements in survival by using acute NIV to treat patients with exacerbations of COPD complicated by acute hypercapnic respiratory failure (AHRF), these patients are at high risk of readmission and further life-threatening events [12, 13]. In a recent study of 110 patients with AHRF (RESCUE study), 65% had another life-threatening event and 49% had died within 1 year after discharge [14].

More recently, however, Köhnlein et al. [15] found a significant reduction of mortality in the treatment arm, and Murphy et al. [16] reported a significant improvement in time to readmission or death (from 1.4 to 4.3 months) and concomitant reduction of 1-year risk of readmission or death by 17% (from 80.4 to 63.4%) for the group receiving home NIV. Additionally, the home NIV group reported a higher quality of life at 3 months, leading the authors to recommend the consideration of home NIV for patients with severe COPD and persistent hypercapnia after a life-threatening exacerbation, but in a very few proportion of patients (6% of the screened patients). Furthermore, the Global initiative for Obstructive Lung Disease (GOLD) 2017 document [17] indicated that home NIV may be considered of some use only in a selected group of patients, particularly in those with pronounced daytime hypercapnia and recent hospitalization.

In summary, home NIV is a complex therapy that has been shown to be of benefit for a number of chronic conditions. In stable COPD, however, the evidence is contradictory and home NIV is currently only suggested for very severe and rare and selected patients [15, 16]. Thus, home NIV in patients with stable COPD continues to be a source of controversy with the concomitant urgent need to develop strategies to reduce the number and severity of exacerbations of COPD.

Currently, two main restraints hamper the development of such strategies, (i) the lack of systematic diagnostic approaches in order to define the underlying pathophysiological phenotype and (ii) the lack of clinical trials on the impact of home NIV in conjunction with pathophysiological phenotypes and their influence on the efficacy/safety ratio. Furthermore, periodical evaluation of compliance, tolerance, and efficacy should be consensual to ensure an adequate delivery of home NIV.

Thus, in order to optimize long-term home NIV, further research is required to identify responders, the relevance of hypercapnic status change in clinical outcomes, the optimum time points for starting home NIV, and equipment settings or hours of ventilation to be efficient. With healthcare objectives and budget constraints, telemonitoring of COPD patients is an important challenge in most European countries.

Therefore, the primary objective of Rescue2-monitor is to test the superiority of any of 3 modalities of home NIV compared to a standard treatment without home NIV (control group) in terms of improving admission-free survival of persistently hypercapnic COPD patients. Furthermore, home NIV with a highly targeted ventilator strategy (“TARGETED HOME VENTILATION” with high level of phenotyping of the patient and high level of monitoring of the quality of the home NIV) will be compared to the other three groups. For the adaptation of this targeted home ventilatory strategy, three main phenotypes are considered as determining factors, (i) OSAHS, (ii) heart failure, and (iii) diaphragmatic dysfunction. For patients without any of these phenotypes, the targeted home ventilatory strategy will be adapted with a high level of monitoring of the quality and purpose of the different settings of the ventilator.

## Methods/design

### Aim and objectives

#### Primary objective

The primary objective of this study is to demonstrate the superiority of any of the three home NIV strategies over standard no-home NIV (only hospital NIV in case of acute respiratory failure) in terms of admission-free survival of COPD patients after an episode of acute respiratory insufficiency with hypoventilation (AHRF) (Fig. 1).

**Fig. 1 Fig1:**
[figure not shown]
Flow diagram of study procedure: *n*_p_ = planned number of patients, V1 to 8 = visit number, T0 to 36 = time in months. For the follow-up visit, the (*) indicates evaluations that are performed if not done previously (at baseline) or if a follow-up is necessary due to abnormal results. Independently of abnormal results, spirometry will be repeated at V2 (T3) or V3 (T6)

#### Secondary objectives

The secondary objectives of the study are to demonstrate for severe COPD patients after an episode of acute respiratory insufficiency with hypoventilation, that any of the three home NIV strategies are superior to standard no-home NIV in terms of:
Global survivalExacerbations frequencyComorbidityQuestionnaires (quality of life, sleep, and dyspnea)(Serious) adverse event (AEs and SAEs) occurrence rateCost-effectiveness

### Study design

Rescue2-monitor is an open-label, prospective randomized, controlled, superiority clinical trial, performed in patients with hypercapnic chronic obstructive pulmonary disease post-acute hypercapnic exacerbation (ClinicalTrials.gov Identifier: NCT03890224).

Four arms (randomization to groups in a ratio of 1:1:1:1) will be compared, i.e., no-home NIV (hospital NIV/control group) versus any of 3 modalities of nocturnal home NIV (test groups). The 3 test treatments are non-targeted home NIV, targeted home NIV, and rescue home NIV (Fig. 2).

**Fig. 2 Fig2:**
[figure not shown]
Study design. Treatment arms are randomized in a 1:1:1:1 ratio

### Study setting

The study is an international multicenter study involving 13 hospitals in France, 20 hospitals in Spain, and 8 hospitals in Portugal. Further, centers are envisaged in Italy. Within a recruitment period of 2 years, a total of 400 patients (100 patients per treatment arm) will be recruited during standard hospitalization after an acute exacerbation (between 2 and 15 days after the acute exacerbation).

### Study population

COPD patients will be recruited during standard hospitalization after an acute exacerbation, based on the following criteria:

#### Inclusion criteria

Patients with COPD, GOLD C or D, and forced expiratory volume in 1 s (FEV1) < 65%ARHF (pH < 7.35 and PaCO_2_ ≥ 45 mmHg (≥ 6 kPa) treated more than 24 h with ventilation (non-invasive or invasive)48 h to 2 weeks with pH > 7.35, and PaCO_2_ ≥ 45 (≥ 6 kPa) after NIV withdrawal, during daytime at rest without oxygen or ventilatory support (or with O_2_ if patients are not able to avoid O_2_ with immediate desaturation below 80%)

#### Exclusion criteria

Patient treated with chronic NIV or CPAP, with ongoing treatmentPrimary diagnosis of restrictive lung disease causing hypercapnia, i.e., obesity hypoventilation and chest wall disease; however, these patients will be included if the FEV1/FVC ratio is < 60% and the FEV1 < 50% if the predominant defect is considered to be obstructive by the center clinicianBMI > 35 kg/m^2^Sedative medication causing hypercapnia (> 3 drugs or more than 20 mg of morphine/day)Polygraphic diagnosis of obstructive sleep apnea syndrome (AHI > 30/h)Cognitive impairment that would prevent informed consentPregnancyTobacco use < 10 pack-yearPsychiatric disease necessitating anti-psychotic medication, ongoing treatment for drug or alcohol addiction, persons of no fixed abode post-dischargeUnstable coronary artery syndromeAge < 18 yearsInability to comply with the protocolExpected survival < 12 months due to any situation other than COPD diseaseDuration of ICU stay > 10 days for this exacerbationNot affiliated to national health insuranceMeasure of legal protection (guardianship, wardship, or judicial protection) for patients over the age of majority.

Screen failures (screened patients who finally do not match all criteria) are collected in the eCRF with the reason for non-inclusion.

Recruitment of patients was halted throughout the confinement period of the COVID pandemic 2020. In case of further confinements, the study period will be extended.

### Medical devices used during the study

The medical devices used to study home ventilation strategies will be home ventilators, which are routinely used at home to ventilate patients with chronic hypoventilation (CE-, ISO marked). Consequently, the investigators will be free to use the ventilator of their choosing based on the suitability and comfort for the patient, but ventilators with tools for monitoring the quality of NIV are mandatory.

As during standard care, the patients will receive an educational session at each visit, to be shown how to use the ventilator in case of an acute problem. Devices will be maintained by home providers, who will be available 24 h 7 days a week in case of technical problems in all the 4 countries.

### Informed consent

The participant’s free and informed consent will be obtained in writing by the principal investigator or by a doctor representing the investigator before enrolment into the study. The person will be given sufficient information and time to give an informed consent. To this end, the participant will be handed out the patient information sheet in his native language and a copy of the informed consent form (SI 1), which must be signed in order to be enrolled. If it is physically impossible for the patient to consent in writing, his or her consent will be confirmed by a third party. This third party will have no connection with the investigator or with the sponsor.

The investigator will specify the methods and circumstances of the informed consent in the study participant’s medical file and retain one original of the signed and dated consent form while a second original will be handed to the participant.

### Randomization

Consenting patients matching the inclusion criteria will be randomized to one of the four treatment arms using a centralized, secure, computer-generated, interactive, web-response system accessible from each study center. The randomization will be balanced by blocks of variable and undisclosed size and stratified on the center.

As the effectiveness of blinding has limited scientific justification for this approach, the unblinded trial design and lack of a sham device, with blinded assessment in terms of the outcome, is consistent with other clinical trials in this field [15].

### Study procedure

The study will be performed in accordance with Good Clinical Practice (GCP) guidelines and international and national regulations in force. The study procedures are presented in Table 1.

**Table 1 Tab1:** Applicability of procedures per study visit. *V0–V8* study visits, *M1–M36* visit time in months, *1D/15D* visit tolerance in days, *1* if not done previously, *2* if follow-up necessary, *3* hand-out of diary; * only for 3 home NIV arms

Visits	VO Baseline	V1 M1±5D	V2 M3 ±15D	V3 M6±15D	V4 M12±15D	V5 M18±15D	V6 M24±15D	V7 M30±15D	V8 M36±15D
Patient information and consent	x								
Inclusion/exclusion criteria	x								
Demographic data	x								
Medical history	x								
Clinical examination									
• Spirometry	x	1/2	1/2						
• 6-minute walk test	x	x	1						
• Diaphragmatic dys function	x								
QoL questionnaires	x	x	x	x	x	x	x	x	x
QoS questionnaires	x	x	x	x	x	x	x	x	x
Dyspnea questionnaire	x	x	x	x	x	x	x	x	x
Charlson comorbidity	x								
Tobacco use	x	x	x	x	x	x	x	x	x
Exacerbations	3	x	x	x	x	x	x	x	x
Laboratory tests									
• Blood gases (PaO2, PaCO2, SpO2)	x	x	x	x	x	x	x	x	x
• PTCO2	x	x	x	x	x	x	x	x	x
• Poly(somno)graphy	x		2						
• Cardiac echography	x		2						
Randomization	x								
Fitting/Settings of ventilator*	x	x	x	x	x	x	x	x	x
Concomitant medication	x	x	x	x	x	x	x	x	x
Device data *		x	x	x	x	x	x	x	x
Adverse events/ hospitalizations		x	x	x	x	x	x	x	x
Educational session	x	x	x	x	x	x	x	x	x

#### Baseline visit

This visit will be conducted by a pulmonologist between 2 days and 2 weeks post normalization of pH following an acute exacerbation and after the results of spirometry and/or polygraphy, if needed. It will include the following procedures:
Patient information and informed consentVerification of inclusion and non-inclusion criteriaRecording of demographic dataRecording of personal medical history
o No continuous positive airway pressure (CPAP) or home ventilator used at home in the last past 6 monthso List of medications (to eliminate more than 3 sedative medications or more than 20 mg of morphine)o No other disease other than COPD with expected survival < 12 monthso Assessment of tobacco use (> 10 packs per year)Clinical assessment:
o Vital status (height, weight, BMI)o Functional respiratory test (spirometry, lung volume, lung diffusion, Pimax, SNIP)o 6 min walk testo Clinical signs of diaphragmatic dysfunctionQuestionnaires
o Quality of life (QoL) and quality of sleep (QoS) scoreso Dyspnea questionnaireo Charlson comorbidity questionnaireRecording of number of exacerbations during the past monthLaboratory tests
o Arterial blood gases (ABG): performed on air > 20′, except if immediate desaturation < 80% or bad tolerance: pH, HCO_3_^−^, PaO2, PaCO_2_, SpO_2_o Nocturnal oximetry with PTCO_2_o Poly (somno)graphyo Cardiac echography (site measurement and central assessment)Hand-out of patient diary to follow exacerbations at home and write the treatment receivedRandomization to NIV treatment armFitting patients with ventilators approved for COPD, ventilator settings, and tolerabilitySetup of NIV in the pulmonology ward for the 3 groups with NIV following last recommendations of setting (high pressure with the aim to decrease PaCO_2_) [14–16]Educational session on usage of home ventilation device

#### Follow-up visits M1

This visit will be conducted at the hospital by a pulmonologist at 4 weeks ±5 days after baseline visit. It will include the following procedures:
Clinical assessment as during baseline visit (spirometry only if not done previously or follow-up necessary)Laboratory tests
o Arterial blood gases (ABG): performed on air > 20′, except if immediate desaturation < 80% or bad tolerance: pH, HCO_3_^−^, PaO_2_, PaCO_2_, SpO_2_o Nocturnal oximetry with PTCO_2_Questionnaires
o QoL and QoS scoreso Dyspnea questionnaireAssessment of tobacco useRecording of number of exacerbations since last visit and diary exacerbations assessmentConcomitant medicationsRecording of adverse events (type, severity, need for hospitalization)Recording of hospitalizations (number high-dependency unit (HDU) or ICU, reasons, length of stay)Verification if primary endpoint has been reached

For the 3 home NIV treatment arms:
Device settingsHours of utilization (from the device counter)Grenoble score for NIV tolerabilityAdjustment of ventilator settings, if necessary and test on the patientEducational session on usage of home ventilation device

For the targeted home NIV treatment arm:
Adjustment of ventilator settings according to algorithm published by Janssens et al. [18]Fragmental use of the ventilation (> 3 stops/night) (ventilator software)Clinical relevant leaks (median and mean)Apnea/hypopnea (AH); if yes, index of the 4 last weeks

#### Follow-up visits M3 to M36 and emergency visits

These visits will be conducted at the hospital by a pulmonologist at the given time point ±2 weeks after baseline visit. It will include the following procedures:
Clinical assessment as during baseline visit (walk test and spirometry at M3 only if not done previously or follow-up necessary)Laboratory tests:
o Arterial blood gases (ABG): performed on air > 20′, except if immediate desaturation< 80% or bad tolerance: pH, HCO_3_^−^, PaO_2_, PaCO_2_, SpO_2_o Nocturnal oximetry with PTCO_2_o Poly (somno) graphy (only at M3 if follow-up necessary)o Cardiac echography (site measurement and central assessment) (only at M3 if follow-up necessary)Questionnaires
o QoL and QoS scoreso Dyspnea questionnaireAssessment of tobacco useRecording of number of exacerbations since last visit and diary exacerbation assessmentConcomitant medicationsRecording of adverse events (type, severity, need for hospitalization)Recording of hospitalizations (number HDU or ICU, reasons, length of stay)Verification if primary endpoint has been reached

For the 3 home NIV treatment arms:
Device settingsHours of utilization (from the device counter)Grenoble score for NIV tolerabilityAdjustment of ventilator settings according to algorithm, if necessary and test it on the patientEducational session on usage of home ventilation device

For the targeted home NIV treatment arm:
Fragmental use of the ventilation (> 3 stops/night) (ventilator software)Clinically relevant leaks (median and mean)Apnea/hypopnea (AH); if yes, index of the 4 last weeks

#### End-of-study visits at M36 or time of readmission/death (primary endpoint)

If at M36 primary endpoint has not been reached:
According to follow-up visits

If primary endpoint reached:
Recording of primary endpoint
o Readmission yes/no; time of readmissiono Death yes/no; time of death

### Assessment of treatment

An electronic CRF (eCRF) and a patient diary will be used to collect all data.

#### Primary endpoint: admission-free survival

Admission-free survival is defined as time from randomization to hospital admission in relation with severe exacerbation of COPD or death by any cause, whichever event occurred first. If neither event occurs, time from randomization to the last known follow-up visit will be considered. If withdrawal occurs prior to readmission or death, time from randomization to withdrawal will be considered.

All readmissions of recruited patients to the hospital, including ICU, emergency ward and pulmonary or internal medicine ward admissions will be followed up by the investigators. A COPD-related hospital admission is defined by worsening respiratory symptoms (cough, wheeze, increased sputum production, increased volume of sputum, and/or increased breathlessness), as assessed by the senior physician, leading to treatment for an acute exacerbation of COPD on the day of hospitalization.

Acute NIV will be introduced at pH < 7.35 and PaCO_2_ > 45 mmHg or if RR > 23 persisting after bronchodilators and controlled oxygen therapy (BTS guidelines and Cochrane review 2017). This introduction of NIV is mandatory to fulfill the “readmission” criterion and will be considered as the primary endpoint reached.

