#### Primary endpoint: admission-free survival

Admission-free survival is defined as the time from randomization to hospital admission or death. Each comparison will be done with a two-sided log-rank test.

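### The primary endpoint is defined inconsistently, and its mandatory NIV condition is undefined for admitted patients already on home NIV, so events can be ascertained differently by arm

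*Protocol article*

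**What the plan says.** The protocol article defines the primary endpoint under the same heading, Primary endpoint: admission-free survival, in two places.

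- **Under Assessment of treatment.** The event is "time from randomization to hospital admission in relation with severe exacerbation of COPD or death by any cause, whichever event occurred first". A COPD-related admission is identified by worsening respiratory symptoms, "as assessed by the senior physician, leading to treatment for an acute exacerbation of COPD on the day of hospitalization". The last paragraph gives triggers for acute NIV: a pH and PaCO2 condition, "or if RR > 23 persisting after bronchodilators and controlled oxygen therapy". It then adds "This introduction of NIV is mandatory to fulfill the" readmission criterion, and says this counts as the primary endpoint reached.
- **Under Statistical analysis.** "Admission-free survival is defined as the time from randomization to hospital admission or death". There is no COPD condition and no NIV condition.

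Three other statements bear on this. The title describes the trial as "comparing hospital- versus home-based acute non-invasive ventilation". The Randomization section describes an unblinded design "with blinded assessment in terms of the outcome". Calculation of sample size assumes 1-year admission-free survival of 35% (control) and 55% (home NIV) without saying which event definition those figures describe.

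**The concern.** An analyst could follow either section, cite the protocol, and analyse a different set of events. In an open-label trial, that choice should not remain open.

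The NIV condition raises a second problem. What makes a readmission count is an action, the introduction of NIV, and NIV is also what the arms differ in. A control patient has no ventilator at home, so acute NIV in hospital is plainly an introduction. A home-NIV patient admitted with the same exacerbation may continue or intensify existing ventilation, and the article does not say whether that qualifies. If it does not, home-NIV arms lose events because of allocation rather than benefit. The point concerns only patients who are admitted: an admission truly avoided by home ventilation is a treatment effect.

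**Working it through.** **1. The definitions side by side.** A is the opening definition under Assessment of treatment, B adds the mandatory NIV condition, and C is the Statistical analysis definition.

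| Situation | A | B | C |
|---|---|---|---|
| Exacerbation admission, acute NIV started | event | event | event |
| Exacerbation admission, no NIV | event | no event | event |
| Exacerbation admission, own home NIV continued or intensified | event | not defined | event |
| Exacerbation admission, intubated directly or NIV refused | event | no event if read literally | event |
| Admission not related to COPD | no event | no event | event |
| Death | event | event | event |

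Only the first and last rows agree. The third row can arise only for patients with a home ventilator.

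**2. The plan's own figure.** Inputs from Calculation of sample size: 35% and 55% at 1 year, 2 years' accrual, minimum follow-up 12 months, 93 per group, familywise error rate 5%. With exponential survival:

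- control hazard = −ln(0.35) = 1.050 per year
- home-NIV hazard = −ln(0.55) = 0.598 per year
- hazard ratio (HR) = 0.598 / 1.050 = 0.569

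Simulating four arms with uniform accrual, 1 to 3 years of follow-up, no dropout, two-sided log-rank tests and the article's three-step chain procedure (4,000 trials) gives 80.3% power for all three comparisons. The stated 93 per group for 80% reproduces.

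**3. What unequal counting would do (illustration).** Assumptions that are not in the documents: no true effect; a death hazard d before readmission of 0.15 to 0.35 per year; a fraction m of readmissions uncounted in each home-NIV arm; all deaths counted. With 100 per arm and control hazard 1.050:

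apparent HR = 1 − m × (1 − d / 1.050)

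The bracket is 0.857 for d = 0.15 and 0.667 for d = 0.35.

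| m | Apparent HR | Chance of at least one significant arm |
|---|---|---|
| 0 | 1.00 | about 5% |
| 10% | 0.91–0.93 | about 7–9% |
| 20% | 0.83–0.87 | about 16–24% |
| 30% | 0.74–0.80 | about 31–53% |

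The last column is simulated with the same chain procedure; ranges span the two death hazards and repeated runs. A cruder version that thins all events, deaths included, with 93 per arm gives 10%, 31% and 62%. The size depends on the model as well as on m.

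**The case against.** **One definition, narrowed in steps.** The text under Assessment of treatment can be read as a severe-exacerbation admission, then what makes it COPD-related, then the operational criterion. That reading is fair and reduces three event sets to two. It leaves the conflict with the Statistical analysis section, which is worded as a definition and carries neither restriction. An unseen analysis plan does not cure this, because the article states the endpoint both ways.

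**Ascertainment is not shown to be unequal.** A reader might infer that events are in fact under-counted in the home-NIV arms and that the comparison is biased towards home NIV. The documents do not support that. The triggers are worded identically for all arms, the text speaks of acute NIV rather than nocturnal home NIV, and nothing says that a home-NIV patient who meets the triggers goes uncounted. Direction is open too: familiarity with NIV could make acute NIV easier to start in those arms and add events. Intubation and refusal have no stated link to allocation. What stands is that the mandatory element is the act, not the measurement, and the act is undefined for patients already ventilated at home.

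**The event rate.** A reader might also infer that the NIV condition pushes control events below the planned 65% (100% − 35%) and leaves the trial underpowered. That does not follow. The 35%/55% are tied to no definition. The Background reports 65% with a further life-threatening event within a year in an earlier study of 110 patients, and 80.4% for readmission or death without home NIV in another trial. The planned 65% may already describe a narrow endpoint.

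**Blinding.** Judgement by the senior physician at admission does not exclude later blinded assessment, and an article may leave adjudication detail to the full protocol. This is a statement to reconcile, not a demonstrated contradiction.

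**Conclusion.** The point holds as an inconsistency in the primary endpoint, with a credible and unaddressed risk of differential ascertainment. The inconsistency is in the text and needs no assumption: an exacerbation admission without NIV and a non-COPD admission are each classified differently depending on the section followed. The risk rests on two documented facts, that introducing NIV is mandatory for a readmission to count and that the term is not defined for patients already on home NIV, in an open-label trial. Its occurrence, size and direction cannot be taken from the documents. The simulated false-positive rates show only that modest unequal counting would matter; the 10–30% fractions and the death hazards are assumed. No sample-size error is claimed. Because the primary result is not uniquely defined as written, this should be settled before analysis.

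**What to change.** Use one event definition in both sections, applied identically in all arms and not dependent on whether NIV is newly started. Two options meet this:

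1. Count every admission that meets the article's existing COPD-related definition, or death.
2. If a ventilatory-failure criterion is kept, count an admission when the protocol's own stated triggers, including the respiratory-rate trigger, are recorded as met, whether NIV is started, continued, intensified, refused or bypassed by intubation.

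Option 1 relies on the senior physician's unblinded judgement; option 2 leans more on recorded measurements. Either way:

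- report any-cause admission or death as a pre-specified sensitivity analysis;
- state which definition the 35%/55% refer to;
- reconcile the blinded-assessment statement in Randomization with the physician-assessed endpoint.

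This concerns what is counted as an event; it implies no change to when NIV is given.

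The cost is a wording amendment and one derived variable. All readmissions are already to be followed up. Blood gases are listed for study and emergency visits but not explicitly for each admission, so option 2 may need an added eCRF field for admission blood gases and respiratory rate. Option 1 pools events with and without acute NIV; the split can be reported.
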